# Prior balloon valvuloplasty versus DIRECT transcatheter Aortic Valve Implantation (DIRECTAVI): study protocol for a randomized controlled trial

**DOI:** 10.1186/s13063-017-2036-y

**Published:** 2017-07-04

**Keywords:** Transcatheter aortic valve implantation (TAVI), Balloon aortic valvuloplasty, Procedural success, Safety, Randomized clinical trial

## Abstract

**Background:**

Balloon predilatation of the aortic valve has been regarded as an essential step during the transcatheter aortic valve implantation (TAVI) procedure. However, recent evidence has suggested that aortic valvuloplasty may cause complications and that high success rates may be obtained without prior dilatation of the valve. We hypothesize that TAVI performed without predilatation of the aortic valve and using new-generation balloon-expandable transcatheter heart valves is associated with a better net clinical benefit than TAVI performed with predilatation.

**Methods/design:**

The transcatheter aortic valve implantation without prior balloon dilatation (DIRECTAVI) trial is a randomized controlled open label trial that includes 240 patients randomized to TAVI performed with prior balloon valvuloplasty (control arm) or direct implantation of the valve (test arm). All patients with an indication for TAVI will be included excepting those requiring transapical access. The trial tests the hypothesis that the strategy of direct implantation of the new-generation balloon-expandable SAPIEN 3 valve is noninferior to current medical practice using predilatation of the valve. The primary endpoint assessing efficacy and safety of the procedure consists of immediate procedural success and secondary endpoints include complications at 30-day follow-up (VARC-2 criteria). A subgroup analysis evaluates neurological ischemic events with cerebral MRI imaging (25 patients in each strategy group) performed before and between 1 and 3 days after the procedure.

**Discussion:**

This prospective randomized study is designed to assess the efficacy and safety of TAVI performed without prior dilatation of the aortic valve using new-generation balloon-expandable transcatheter heart valves. We aim to provide robust evidence of the advantages of this strategy to allow the interventional cardiologist to use it in everyday practice.

**Trial registration:**

ClinicalTrials.gov identifier: NCT02729519. Registered on 15 July 2016.

**Electronic supplementary material:**

The online version of this article (doi:10.1186/s13063-017-2036-y) contains supplementary material, which is available to authorized users.

## Background

Transcatheter aortic valve implantation (TAVI) is now the standard of care for patients with inoperable severe symptomatic aortic stenosis and an accepted alternative to surgery for high-risk patients [1–6]. The improvement in operator experience and valve technology, combined with better screening and inclusion of lower-risk patients, have resulted in dramatically decreased in-hospital complications after TAVI procedures. However, despite a high procedure success rate (>95%), TAVI has remained associated with complications directly related to the technique (stroke, aortic regurgitation, vascular access bleeding) or to comorbidities frequently associated with aortic valve disease in older and frail patients [3–6]. Reducing periprocedural complications is thereby the key for the future use of TAVI in lower-risk patients. Balloon aortic valvuloplasty (BAV) has been considered as a mandatory step in the TAVI procedure both to facilitate the implantation of the transcatheter heart valve (THV) and to reduce the radial counterforce for optimal device expansion. However, BAV has been shown to carry specific complications and risks [7, 8]. With the development of a new generation of balloon-expandable THVs, associated with low profile and orientable delivery system, the crossing of the valve is facilitated. While both balloon dilatation and the need for post dilatation have been considered to increase the risk of cerebral embolization, avoiding BAV prior to TAVI is attractive and may simplify the procedure [9–12]. Only few nonrandomized studies have shown that direct implantation of the THV is feasible [10, 13, 14], but there are currently no randomized data concerning the safety and efficacy of TAVI performed with new-generation balloon-expandable THVs without prior dilatation of the aortic valve.

DIRECTAVI is the first randomized controlled trial that will evaluate the efficacy and safety of direct implantation of a balloon-expandable new-generation prosthesis, the Edwards SAPIEN 3 THV.

## Methods/design

DIRECTAVI is a prospective, randomized, monocentric, open-label trial that aims to test the hypothesis that TAVI performed without predilatation (test arm) and using the new-generation balloon-expandable Edwards SAPIEN 3 THV is associated with a better net clinical benefit in comparison to procedures performed with predilatation (control arm). The trial has an intentional noninferiority design concerning the primary endpoint. From an ethical standpoint, a sham procedure in the no-dilatation control arm could not be countenanced. The study is conducted in the academic University Hospital of Montpellier, France. The study flow chart is presented in Fig. 1.

**Fig. 1 Fig1:**
[figure not shown]
Flow chart of the study. *BAV* balloon aortic valvuloplasty, *MDT* multidisciplinary heart team, *MACCE* major adverse cardiovascular and cerebral events

### Patient population and procedure

The study population consists of 240 patients who will have TAVI via a transvascular or transthoracic approach. Patients should be deemed eligible for TAVI by a multidisciplinary team including at least an interventional cardiologist, a cardiothoracic surgeon and an anesthetist. All the procedures performed with the third-generation balloon-expandable Edwards SAPIEN 3 THV (Edwards Lifesciences, Irvine, CA, USA) will be considered for inclusion in the study. The SAPIEN 3 THV system is a new generation of balloon-expandable THVs which incorporates various new features to facilitate implantation and minimize vascular injury, stroke, suboptimal positioning, and paravalvular regurgitation [15]. The prosthesis size (23, 26 or 29 mm) and the access route (transfemoral, transcarotid, subclavian or transaortic) are left to the discretion of the operating team. For all patients, both vascular access and aortic valve apparatus are evaluated before the procedure with multislice computerized tomographic angiography (MSCT) of the entire aorta using vascular windows settings. The transfemoral access is the first choice when possible.

Main procedures are done under mild sedation and local anesthesia in our center. Low-profile 14 to 16 French delivery systems are used in all patients with an almost exclusive surgical vascular access. For femoral or carotid access, we use a surgical “preclose technique” in order to avoid arterial cross-clamping and the purse-string effect [16]. For the control group, BAV will be performed with a balloon of 18, 20 or 22 mm diameter according to the THV size. All patients will receive 0.5 mg/kg heparin at the time of introducing the femoral sheath to achieve an activated clotting time of >250 s. All TAVI procedures are performed in the same site by six medical teams comprising at least one interventional cardiologist and a cardiac surgeon, assisted by one nurse for valve-crimping, a nurse who assists the anesthetist and a technician from the catheterization laboratory. A combination of clopidogrel 75 mg and aspirin 75 mg is introduced in all patients after the procedure except in those with an indication for vitamin k antagonists or direct anticoagulant therapy who had only aspirin 75 mg. The vitamin K antagonists or direct orally administered anticoagulants are always stopped at least 2 days before the procedure and usually reintroduced 1 day later.

### Study design

#### Inclusion/exclusion criteria

According to the inclusion and exclusion criteria summarized in Table 1, the study investigators will confirm patient eligibility. All patients who are referred for TAVI in our center and who meet the inclusion criteria will be successively included and randomized. After verification of the eligibility criteria and obtaining informed consent, the patients will be randomized by an investigator to receive either BAV or direct implantation of the valve. For this purpose, the investigator will connect to the secure and dedicated CLINSIGHT website (CS Online) with his username and personal password. The random allocation sequences will be computer-generated by an independent statistician using a 1:1 ratio and permuted blocks of 4 and 6.

**Table 1 Tab1:** Eligibility criteria for the transcatheter aortic valve implantation without prior balloon dilatation (DIRECTAVI) study

Criteria	Definition
Inclusion criteria	
Patients aged ≥18 years	
Severe aortic valve stenosis	Mean gradient ≥40 mmHg or aortic valve area <1 cm^2^ on TTE^a^
Symptoms suggestive of severe aortic stenosis	Dyspnea, heart failure, angina, syncope
Contraindication for open heart surgery or excessive surgical risk	Decision of the multidisciplinary heart team
TAVI using the balloon-expandable SAPIEN 3 valve	
Vascular access	Transfemoral, transcarotid, transaortic or subclavian access
Exclusion criteria	
Preexisting aortic prosthesis	“Valve in valve” technique
Transapical access	
BAV^b^ performed for less than 1 week	
Recent myocardial infarction	Within the last 3 months
Left ventricular or atrial thrombus	TTE evaluation
Significant mitral or tricuspid regurgitation	>grade II on TTE
Recent cerebrovascular event	Within the last 3 months
Carotid or vertebral arterial narrowing	Stenosis >80% (Doppler or CT scan)
Active internal bleeding	
Thrombocytopenia	Platelet count <50,000/mm^3^
Lack of written informed consent	
Severe mental disorder, drug/alcohol addiction	Specialized evaluation
Life expectancy <1 year	
Participation in another drug or device study	Any study that would jeopardize
	the appropriate analysis of study endpoints
High probability of nonadherence to the follow-up	Social, psychological or medical requirement reason
Pregnancy	

^a^
*TTE* transthoracic echocardiography, ^b^
*BAV* balloon aortic valvuloplasty. *CT* computed tomography

### Data collection and follow-up (see Fig. 2)

**Fig. 2 Fig2:**
[figure not shown]
The transcatheter aortic valve implantation without prior balloon dilatation (DIRECTAVI) trial

Baseline data collected from enrolled patients will include demographics, past medical history, previous cardiac investigations and current medication. Patients will undergo transthoracic echocardiography at baseline, post procedure and at 1-month follow-up. Prospective monitoring of adverse and clinical events starts at randomization and continues until 1 month. All major adverse cardiovascular and cerebrovascular events (MACCE) and other serious adverse events will be recorded in the electronic Case Record Form and reported to the coordinating center within 3 days of first identification. On receipt of notification of any adverse or clinical event, the coordinating center will request additional details, specific to the nature of the event. These episodes will be carefully monitored by the trial coordinator and will be part of the information provided at regular intervals to the Clinical Events and Data Monitoring and Ethics Committees. The Clinical Events Committee will be blinded to treatment and will consider each MACCE or adverse event reported and ratify occurrence of an endpoint according to the study definitions.

This 1-month visit is part of the routine practice after TAVI. A consultation appointment will be given to patients when they will be discharged from the hospital, and a dedicated research assistant will call the patients who did not attend on the day after their missed visit. In case of inability for the patient to come, the research assistant and/or investigator will contact the patient GP or cardiologist to obtain some clinical information on the patient. All concomitant care or interventions are permitted during the study follow-up.

### Study endpoints

The primary endpoint, assessing efficacy and safety of the procedure, consists of immediate procedural success defined as the absence of immediate procedural mortality *and* correct positioning of a single prosthetic heart valve into the proper anatomical location *and* intended performance of the prosthetic heart valve (no prosthesis-patient mismatch and mean aortic valve gradient <20 mmHg or peak velocity <3 m/s), *and* no moderate or severe prosthetic valve regurgitation [17].

According to Valve Academic Research Consortium (VARC-2) criteria immediate procedural mortality is defined to capture intraprocedural events that result in immediate or consequent death ≤72 h post procedure [17].

Secondary endpoints include cardiovascular and all-cause mortality, procedure outcomes (length of procedure, incidence of post dilatation, radiation exposure, contrast volume injection), and adverse events (VARC-2 criteria) at 30-day follow-up. Adverse events considered included life-threatening/major/minor bleeding, vascular access complications, acute kidney failure (RANKIN classification stage 2 or 3), pacemaker implantation, neurological events or new hospitalization for cardiac causes. We will also evaluate duration of hospital stay, echocardiography data (transvalvular gradients, aortic regurgitation quantification, left ventricular systolic and diastolic parameters). All the definitions used are in accordance with the VARC-2 guidelines [17].

### Potential biases and prevention

Our study is prone to a number of biases. Since the investigator cannot be blinded during the study, the measurements of the primary outcome components will be made by an independent and blinded cardiologist as follows:Absence of immediate procedural mortality: death of the patient during or within 24 h of the procedureCorrect positioning of a single prosthetic heart valve into the proper anatomical location in the aortic ringNo prosthesis-patient mismatch (conformity between the size of the prosthesis and the size of the annulus ring) and mean aortic valve gradient <20 mmHg or peak velocity <3 m/s), *and* no moderate or severe prosthetic valve regurgitation. This evaluation using echography and Doppler at 24 and 72 h post procedure will be made by the blinded cardiologist. A potential selection bias will be minimized by the enrollment of all consecutive patients who meet the eligibility criteria

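### The mortality part of the primary endpoint has two conflicting definitions, which differ in both time window (72 h or 24 h) and causal condition

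*Protocol article*

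**What the plan says.** The protocol article describes the mortality component of the primary endpoint in two places.

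- **Study endpoints.** The primary endpoint is "immediate procedural success defined as the absence of immediate procedural mortality", together with correct positioning of a single valve, intended valve performance and no moderate or severe regurgitation. Citing VARC-2, the section says that the mortality term captures "intraprocedural events that result in immediate or consequent death ≤72 h post procedure". It closes with "All the definitions used are in accordance with the VARC-2 guidelines".
- **Potential biases and prevention.** Because the investigator cannot be blinded, "the measurements of the primary outcome components will be made by an independent and blinded cardiologist as follows". The first item in the list is the mortality component, described as "death of the patient during or within 24 h of the" procedure. The same list puts the echocardiographic assessment at 24 and 72 h.

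A second body is also involved. Data collection and follow-up, and Study management, give the adjudication of clinical events to a blinded Clinical Events Committee, which is to apply the study definitions. The article does not say whether those are the definitions under Study endpoints or the cardiologist's list.

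**The concern.** Both texts are current, both concern the same component of the only primary endpoint, and neither is presented as a deliberate departure from the other. They differ in two respects: how long after the procedure a death counts, and whether it must follow from something that happened during the procedure.

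Two blinded bodies could therefore classify the same death differently, each following the protocol. If the conflict is noticed only after events are known, someone in an open-label trial will choose the rule knowing what it does to the result. With 95% success assumed, about 0.05 × 120 = 6 failures per arm are expected, so one or two reclassified patients are not negligible against a 7-point margin.

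**Working it through.** **Step 1. The two rules side by side.** The table asks whether the mortality component is failed, in a patient who otherwise meets the valve criteria.

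| Death | Study endpoints rule | Blinded cardiologist's rule | Agree? |
|---|---|---|---|
| Within 24 h, from an intraprocedural event | failure | failure | yes |
| Within 24 h, not from an intraprocedural event | not counted | failure | **no** |
| At 24-72 h, from an intraprocedural event | failure | not counted | **no** |
| At 24-72 h, not from an intraprocedural event | not counted | not counted | yes |

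A patient who fails a valve criterion is a failure under both rules, so the conflict does not matter there.

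**Step 2. Inputs.** From Sample size determination: control success 95%, margin 7%, power 80%, significance level 5%, N = 240. From Statistical analysis: a one-sided Farrington-Manning method. From the eligibility and randomisation text: 1:1 allocation, so 120 per arm. Noninferiority is taken to mean that the direct-implantation arm is not worse by 7 points or more. The rate of deaths in the two disputed rows is not given anywhere, so the effect below is per death and is not a forecast.

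**Step 3. The plan's own figure.** With equal success rates of 95% and a one-sided 5% level:

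n per arm = 2 × 0.95 × 0.05 × (1.645 + 0.842)² / 0.07² = 119.9, rounded up to 120, so N = 240.

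The stated figure reproduces, and it does not depend on which death rule is used.

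**Step 4. Effect of one reclassified death.** In one arm it moves the success rate, and so the difference, by 1/120 = 0.83 points. As a share of the margin this is 0.83/7 = 12%.

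**Step 5. Where the decision turns.** The Farrington-Manning statistic is z = (p_direct − p_control + 0.07) / SE, with SE computed from rates restricted to differ by the margin. Take 6 control failures (114/120 = 95%):

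- 7 direct-arm failures (113/120): z = 0.0617/0.0324 = 1.90, one-sided p = 0.028, noninferior.
- 8 direct-arm failures (112/120): z = 0.0533/0.0328 = 1.63, one-sided p = 0.052, noninferiority not shown.

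One patient separates the two conclusions.

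**Step 6. How often one failure would matter.** Let both arms be binomial with n = 120 and success 95%. Sum the probabilities of all outcome pairs that are noninferior as they stand but not after one direct-arm success becomes a failure. The result is 0.118. This is conditional on exactly one added failure, in the direct arm only.

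**Step 7. Range over assumed rates.** If the choice of rule lowers the true success rate by 0, 1, 2 or 3 patients per 120, the power by the formula behind Step 3 (unpooled variance) is:

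| Patients per 120 | Direct arm only | Both arms equally |
|---|---|---|
| 0 | 80.0% | 80.0% |
| 1 | 67.9% | 74.8% |
| 2 | 54.7% | 70.2% |
| 3 | 42.0% | 66.0% |

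**The case against.** The best defence is that little harm is likely. Disputed deaths are probably few. If they fall equally in both arms, the observed difference does not move. A blinded committee reviews all clinical events, monitoring runs to one month, and dates of death are collected whichever window applies, so the endpoint can be scored again later. All of this stands. It limits the damage but does not say which rule defines the endpoint, and the committee has no stated definition beyond the two that conflict.

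A reader might infer several stronger things that the document does not support.

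- **That the cardiologist's rule is simply the more lenient one.** It is shorter in time but broader in cause, so it can also count a death that the declared endpoint would not.
- **That every death at 24-72 h switches category.** Only those arising from an intraprocedural event, in patients otherwise meeting the valve criteria, do so.
- **That such a patient is plainly a success under the 24 h rule.** A patient who dies between the two scheduled echocardiograms has no 72 h reading, so overall status would be unclear. Only the mortality component is certain to differ.
- **That the mismatch criterion also conflicts.** The cardiologist's list glosses it as "prosthesis-patient mismatch (conformity between the size of the prosthesis and the size of the annulus ring". The Study endpoints section prints no mismatch definition, and calling the gloss a departure would need the VARC-2 text, which is not at hand.
- **That the absence of a named deciding echocardiogram is an error.** A condensed article can leave that to the full protocol or analysis plan.
- **That the wording "acute kidney failure (RANKIN classification stage 2 or 3" bears on this point.** It concerns a secondary adverse event and looks like a label slip, with no effect on noninferiority.

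**Conclusion.** The contradiction is real and lies in the primary endpoint, so it has to be resolved before analysis. The textual finding rests on no assumption: two current sections give different windows and different causal conditions for the same component, and nothing ranks them.

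The size is conditional. Each death reclassified in one arm costs 0.83 points, 12% of the margin. The probability of about 0.12 that the conclusion changes assumes 120 per arm, 95% success in both arms, a one-sided 5% Farrington-Manning test and exactly one added failure in the direct arm. It is not the probability that the discrepancy will alter this trial's result. That would also depend on the chance of a disputed death occurring in one arm only, which the protocol does not give.

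**What to change.** Use one definition, stating both the time window and the causal condition, in Study endpoints, in Potential biases and prevention, in the blinded cardiologist's instructions and in the Clinical Events Committee's definitions. The natural choice is the wording already under Study endpoints (deaths up to 72 h that result from intraprocedural events), because it is the declared endpoint and that section says all definitions follow VARC-2. Shortening it to any death up to 72 h would drop the causal condition and match neither section.

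Make the change before any unblinded data are seen. Re-score patients already assessed from the recorded dates and causes of death, and report the other rule as a sensitivity analysis.

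The cost is wording in the protocol, the case report form guidance and the assessor instructions, plus the re-scoring. The sample size of 240 does not change on this ground.

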### Ancillary study

An ancillary substudy will enroll 50 patients (25 in each arm) and will be dedicated to evaluate ischemic cerebral events with diffusion-weighted magnetic resonance imaging (DW-MRI) of the brain performed before and after (within 3 days) the TAVI procedure (between days 2 and 5). All consecutive included patients will be proposed to participate in this ancillary study, and all those agreeing to participate will be enrolled until completion of the sample size. MRI will be interpreted by two experienced radiologists blinded to the timing of the imaging and the neurological status of the patient.

### Ethics

The Regional Ethics Committee has approved the trial (Comité de Protection des Personnes Sud Méditerranée, Montpellier, France) and all patients will provide oral and written informed consent. The trial is conducted according to the World Medical Association Declaration of Helsinki and will conform to the ICMJE Recommendations for the Conduct, Reporting, Editing, and Publication of Scholarly Work in Medical Journals. The trial has a Steering Committee, an independent Event Adjudication Committee, and an external Independent Data Monitoring and Safety Committee (DMSC) (registered number: 2015-A01824-45). The DMSC is composed of an interventional cardiologist, a cardiac surgeon, a neurologist, and a statistician. The trial is registered at ClinicalTrials.gov (NCT02729519).

